### Sample Size Calculation

As the choice of type I errors (α, false positive), type II errors (β, false negative), and effect size may be quite arbitrary [79], we suggest calculating the sample size or power using the *R* value (eHSP-70 to iHSP-70 ratio) for a pilot study (alternatively, owing to feasibility, a preliminary study may be conducted on mice or rats).

Furthermore, as providing a priori sample size calculation is misleading and the presentation of CIs—although serving the same purpose—is superior [80], it would be better to use the CI of the *R* value to calculate the sample size based on the feasibility of a priori assumptions about the study results and available resources. In addition, because foods and drinks may be served and consumed at even wider temperature ranges, it would be instrumental to calculate sample sizes based on wider *R* ranges (approximately 0.2-6).

According to Krause et al [30], assuming the ratio *R* = (eHSP-70) / (iHSP-70) = 1 for the controls (resting and unstimulated) and assuming a moderate-hot meal temperature may produce a shift in *R* to up to 5, which is paralleled by an increase in inflammatory markers and stimulation of cell proliferation, *R* values >5 can be considered as an exacerbated proinflammatory response. However, for a conservative calculation, we suggest using *R=*2*.* According to Hunter-Lavin et al [81], heat-shocked cells simultaneously measured HSP-70 at 37 °C (*R*=1.00), 39 °C (*R*=1.45), 42 °C (*R*=0.65), 43 °C (*R*=0.48), and 45 °C (*R*=1.97), this later temperature confirms a proinflammatory response.

Note that at 45 °C (*R*=1.97), there is a turning point compared with that at 43 °C. This means that if a study intends to investigate wider ranges of meal temperature, it is necessary to calculate an array of expected *R* values and then choose the maximum calculated sample size. For an *R* value between 0.22 and 1.1, a sample size of 9 participants is needed to achieve 80% power [1], whereas an *R* value between 1.8 and 6 would require 75 participants to achieve 90% power [2].

Changes in the calculation of the *R* value are suggested to be valid during heat exposure, as *R* values are associated with the heat exposure of peripheral blood mononuclear cells to different temperatures within a physiological range [30]. Precautions that should be considered could include, but are not limited to, correction for noncompliance of the participants, adjustment for multiple comparisons, and innovative study design.

A total of 80 patients will be randomized equally (1:1:1:1) between the 3 active treatments and the thermoneutral group. Overall, 20 participants will be randomly allocated to the thermoneutral diet group (37 °C): 20 at 42 °C, 20 at 49 °C, and 20 at 54 °C. The primary analysis will be intention-to-treat for the whole study cohort.

It is possible that there are multiple roles of HSPs in body weight, weight regain, and composition, probably related to the exposure time during diet ingestion (and also dietary temperature acclimatization during short-term periods, midterm periods, and long-term periods and presence or absence as well as the degree of insulin resistance in people). Thus, conducting a clinical trial for 12 weeks would provide a sufficient time course to investigate this point.

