There is ample literature on the effects of heat stress on fat deposition [35], insulin sensitivity [36], and the facilitating role of HSPs in adiposity [37-39]. The most direct evidence supporting our hypothesis comes from studies conducted on pigs. Exposure to low or high ambient temperatures directly impacts heat production and energy balance in pigs [40]. Heat stress causes enhanced adiposity [41] and growth performance through reduced energy and nitrogen use [42]. However, it is noteworthy that novel observations challenge this long-held traditional dogma, linking reduced productive output during heat stress to decreased nutrient intake. It is now clear that the heat stress response profoundly changes postabsorptive carbohydrate, lipid, and protein metabolism independently of decreased feed intake through harmonized alterations in fuel supply and use by various tissues [43]. One might argue whether heat stress in pigs is relevant to the effects of food temperature on energy metabolism in humans, especially when there is no direct evidence to show that ingesting hot food raises body temperature to such an extent. In addition, it may be argued that the association of HSPs with obesity does not automatically infer causation, and it is well known that these systems respond to metabolic stress. Therefore, to test this hypothesis, we prepared a short proposal to conduct a clinical trial, as described in the *Methods* section.

Altogether, these trials might provide preliminary evidence that HSPs contribute to obesity and weight regain. There is evidence that other HSPs, that is, HSP-A12A, regulate adipocyte differentiation and diet-induced obesity through positive feedback regulation with PPARγ (peroxisome proliferator-activated receptor gamma) [44].

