### Further Technical Issues That Need to Be Addressed in the Pilot Clinical Trial

One might argue whether the study discriminates between other possible influences of meal temperature on energy balance mentioned in the paper (eg, effect on gastric emptying and diet-induced thermogenesis). Evidently, these issues should also be controlled. Participants can eat ad libitum during the 12 weeks of intervention and are fed only soups for 3 meals a day for 12 weeks and are supposed to stay in the laboratory during the entire experiment. This can confound the assessment of hunger or satiety obtained using the visual analog scale using different meal sizes. If participants receive standardized and isocaloric meals, it can mask a possible effect on appetite as well. A very important issue regarding meal temperature is the experienced pleasantness of the meal, which can influence food intake. This should be assessed as well. We have proposed an intention-to-treat analysis for the pilot study. Such a long intervention probably might result in a significant dropout rate, so it is questionable if sufficient participants will conclude the study.

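### The sample-size section claims 80% power over a range of R that contains the control value, calls R=2 conservative although its own 42 °C value is harder to detect, and gives no basis or unit for 9 and 75

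*Protocol article*

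**What the plan says.** All of this is in the protocol article, Sample Size Calculation, unless another section is named.

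- **Quantity and control value.** The article proposes to size the study on R = eHSP-70 / iHSP-70, with R=1 for resting controls and R=1.00 for cells at 37 °C.
- **Planning value.** After citing a shift in R of up to 5, it continues: "for a conservative calculation, we suggest using" R=2.
- **Temperature-specific values.** It lists R=1.45 at 39 °C, 0.65 at 42 °C, 0.48 at 43 °C and 1.97 at 45 °C, and none above 45 °C.
- **Rule.** For wider temperature ranges, compute a set of expected R values and take the largest resulting sample size.
- **Results.** For an R "value between 0.22 and 1.1, a sample size of 9 participants is needed to achieve 80% power", whereas an R "value between 1.8 and 6 would require 75 participants to achieve 90% power".
- **Allocation.** "A total of 80 patients will be randomized equally (1:1:1:1) between the 3 active treatments and the thermoneutral group", that is, 20 per arm.
- **Error rates.** None are fixed; the section opens with "As the choice of type I errors (α, false positive), type II errors (β, false negative), and effect size may be quite arbitrary".
- **Dropout.** In Further Technical Issues: "Such a long intervention probably might result in a significant dropout rate". No rate is given.

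**The concern.** A power statement for a range of effects should hold at the hardest point of that range. The range given for 9 participants runs through the control value, so its hardest point is no effect at all. The planning value R=2 is presented as cautious. Yet the one active-arm temperature with a listed R (42 °C, an arm in both Measures and Sample Size Calculation) has R=0.65. That is closer to 1 on the log and raw scales, and in the opposite direction.

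9 and 75 are the only results of the sizing exercise. A reader will attach the 90% to the 80 participants actually randomized. If that is not justified, a null result, above all for 42 °C versus 37 °C, could be taken as evidence against the hypothesis when the trial had little chance of detecting the effect.

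**Working it through.** **Inputs.** From the article: control R=1; the R values above; 9 at 80% power; 75 at 90% power; 20 per arm. Not given: alpha, SD, scale, test, and whether 9 and 75 are per arm or total. Assumed here: two-sided alpha 0.05 and a two-sample t test on log R against the 37 °C arm.

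**Formulas.** With n per arm and d = |ln R| / SD, power is the probability that a noncentral t variable with 2n − 2 degrees of freedom and noncentrality d√(n/2) exceeds the two-sided critical value in absolute size. Where an SD is needed, it is solved from the article's own sample size: SD = |ln R| / d*, where d* is the effect that the sample size detects with the stated power.

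**Step 1: reproduce 9 and 75.** This cannot be done from the stated inputs. Solving backwards by the normal approximation on the log scale, 9 at R=0.22 (80%) and 75 at R=1.8 (90%) imply similar SDs: 1.15 and 1.11 if per arm, 0.81 and 0.79 if two-arm totals, 0.57 and 0.56 if four-arm totals. So 75 would fit the hardest end of its range, and 9 the easiest end of its own.

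**Step 2: 9 over the range 0.22 to 1.1.** For 9 per arm and 80% power, d* = 1.407, so SD = |ln 0.22| / 1.407 = 1.514 / 1.407 = 1.08. With that SD and 9 per arm:

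| R | \|ln R\| | d | power |
|---|---|---|---|
| 0.22 | 1.514 | 1.41 | 80% |
| 0.48 | 0.734 | 0.68 | 27.5% |
| 0.65 | 0.431 | 0.40 | 13% |
| 1.00 | 0 | 0 | 5% (alpha) |
| 1.1 | 0.095 | 0.09 | 5% |

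**Step 3: is R=2 conservative?** At equal SD, the required n is proportional to 1/(ln R)². Relative to R=2 (ln 2 = 0.693):

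- R=0.65: (0.693/0.431)² = 2.6 times
- R=1.45: (0.693/0.372)² = 3.5 times (39 °C, not a study arm)
- R=1.97: (0.693/0.678)² = 1.05 times
- R=0.48: (0.693/0.734)² = 0.89 times (43 °C, not a study arm)

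On the raw scale, R=0.65 needs (1/0.35)² = 8.2 times.

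**Step 4: what 20 per arm gives for the effect behind 75.** Bonferroni is for three comparisons with 37 °C.

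| 75 read as | d* at 90% | power, 20 per arm | with Bonferroni |
|---|---|---|---|
| per arm | 0.53 | 38% | 22% |
| two-arm total | 0.76 | 65% | 47% |
| four-arm total (18.75 per arm) | 1.09 | 92% | 82% |

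**Step 5: 42 °C versus 37 °C at R=0.65, 20 per arm.** The SD is anchored to 75 being right at R=1.8 (ln 1.8 = 0.588).

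| 75 read as | log SD = 0.588/d* | d = 0.431/SD | power |
|---|---|---|---|
| per arm | 1.10 | 0.39 | 23% |
| two-arm total | 0.77 | 0.56 | 40% |
| four-arm total | 0.54 | 0.80 | 69% |

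On the raw scale the same exercise gives 11%, 18% and 31%. On the most favourable row (log scale, four-arm total), 90% power needs 35 per arm.

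**Step 6: spare participants.** If 75 is the four-arm total, 80 leaves (80 − 75)/80 = 6.25%. If 20% drop out (an assumption), 16 per arm remain, and the 92% falls to 85%, or 70% with Bonferroni.

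**The case against.** Several points on the other side stand.

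- **No power per comparison is stated.** A reader might infer that 20 per arm fails to deliver the claimed power for each comparison. The article makes no such claim and attaches no power to 80. Taking the maximum sample size and then randomizing 80 fits 75 as a four-arm total, and on that reading an unadjusted comparison with 37 °C keeps 92%. A general shortfall is not shown.
- **9 and 75 do not contradict each other.** It is tempting to say that a range near no effect cannot need fewer people than a range far from it. Step 1 shows that a common log-scale SD accounts for both, and the power levels differ.
- **R=2 is below some cited values.** It follows directly on the shift of up to 5, and it is cautious against that. On the log scale R=0.48 is also a slightly larger effect than R=2. What survives is R=0.65 at 42 °C.
- **The article is condensed.** Both sample sizes carry reference markers, so alpha and SD may be set out elsewhere. That could supply the missing inputs, but it cannot make a range containing R=1 powered.
- **The limits might be two group values to be compared**, 0.22 against 1.1 and 1.8 against 6. The null would then not lie in the range. But the wording is of a value between limits, controls are set at R=1, and the log SDs implied by 9 and 75 would differ (1.22 and 2.27 per arm).
- **Another anchor is possible.** If 9 per arm were enough at R=0.65, 20 per arm would give about 99%. That needs a log SD of 0.431/1.407 = 0.31, against 0.54 to 1.10 behind 75 at R=1.8.
- **The study is called a pilot.** The article prefers confidence intervals, lists noncompliance and multiple comparisons as precautions, and doubts that enough participants will finish. This supports the fix; it does not correct the figures.

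**Conclusion.** The point holds in a limited form.

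- **Firm, whatever the SD:** the claim of 80% power with 9 participants cannot hold over 0.22 to 1.1, because the range contains the control value. R=2 is not the hardest listed case either: 0.65 at 42 °C needs about 2.6 times the sample size on the log scale at equal SD. If R=2 is the planning value, the article's own rule of taking the maximum is not followed.
- **Dependent on the reading:** 20 per arm has 38%, 65% or 92% power for the effect behind 75. The article does not settle which, so neither an underpowered nor an adequately powered design can be asserted in general.
- **Dependent on the SD anchor:** power for R=0.65 at 42 °C is 23% to 69% (log scale) with the SD tied to 75 at R=1.8. It falls short of 90% on all three readings.
- **Thin margin:** five spare participants are few against dropout that the article itself expects to be significant, though it gives no rate to compare with.

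All power figures assume a two-sided 5% level and a t test on R against 37 °C. They are back-solved, not taken from stated variability.

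**What to change.** In Sample Size Calculation:

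1. Delete the claim of 80% power with 9 participants, and the word *conservative* for R=2.
2. Replace the claim of 90% power with 75 participants by what the fixed design delivers for log R against the 37 °C arm, two-sided 5%:

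| | 80% power | 90% power | 95% CI half-width |
|---|---|---|---|
| 20 per arm | 0.91 SD | 1.05 SD | 0.64 SD |
| 20 per arm, Bonferroni for three | 1.06 SD | 1.21 SD | – |
| 16 per arm (assumes 20% dropout) | – | 1.18 SD | – |
| 16 per arm, Bonferroni for three | – | 1.37 SD | – |

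3. State that the number is per arm, name the dropout assumption, and present the study as a pilot sized for precision, which is the section's own preference.

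The cost is wording and a less favourable stated figure. No participants are added, and the article reports that the trial has not been initiated.

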### A Proposal to Conduct an RCT

A 4-arm randomized design investigating diets served at different temperatures in 5 °C increments (with core body temperature as a reference) in healthy adults would be the first step to elucidate the potential mechanism linking higher meal temperature with energy contribution. The same protocol can be replicated in patients who are overweight and obese or in people with T2DM. In addition, a crossover design can be performed with necessary modifications.

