### Participants: Inclusion and Exclusion Criteria

The participants will include 80 healthy (BMI 25-35 kg/m^2^) men and women aged 19-65 years. Entry criteria will include people who are not currently dieting to lose weight and have had no weight loss or gain >2 kg over the past 3 months; not taking any medications (including antifever) that affect energy expenditure or eating; not using tobacco; not pregnant or lactating or planning to become pregnant in the next 12 months; and have no limitations to eating specific foods or to swallowing (eat and drink) a normally estimated range of meal temperatures (37-52 °C). The participants must not have major health problems; known cardiovascular (cardiac, peripheral vascular, and cerebrovascular), pulmonary (chronic obstructive pulmonary disease, interstitial lung disease, and cystic fibrosis), or metabolic (diabetes, thyroid disorders, and renal or liver disease) disease; and severe fever.

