### Procedures

The day before the experimental session, the participants will be instructed to avoid alcohol, caffeine, and strenuous exercise and to drink plenty of water for 24 hours. On the day of the experimental session, the participants will be asked to arrive at the laboratory adequately rested and will be provided with boluses of soups (each 100 ml) with a predefined temperature to be taken once (to overcome the problem of temperature dissipation).

The energy content of bolus diets (including the thermoneutral diet and temperature-graded bolus diets) will be matched to each of the participant’s objectively calculated energy demands [62] and will be provided in the following manner: 20% energy for breakfast, 50% for lunch, and 30% for dinner. This procedure will facilitate the administration of boluses with graded temperatures (eg, +5 °C increments) with a fair precision from 37 °C to 52 °C, which is both ethical and within the optimal drinking temperature of 57.8 °C and <85 °C for the maximum temperature used to serve hot drinks such as coffee [63].

After assuring sufficient hydration (urine-specific gravity <1.025) [64], the participants will be instrumented in a thermoneutral room (approximately 25 °C) and then will be entered into a whole-body calorimeter regulated to 35 °C with approximately 20% relative humidity, where they will rest in an upright seated position for a 30-minute habituation period while steady-state measurements will be obtained.

The dietary temperature will be measured using a noncontact thermometer. All drinks and a standardized diet will be served at room temperature to maximize gastric emptying and fluid uptake while minimizing diuresis. It is expected that by using this metered intake to control for intake pacing, ingestion will be completed between 3 minutes and 5 minutes and will control for heat dissipation of foods and fluids as well. To avoid thermal injury while providing a satisfactory sensation to the participants, the optimum temperature for serving hot fluids and meals will be observed [63].

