### Measures

All outcome measures will be measured at 0, 6, and 12 weeks. The participants will be asked to follow their assigned diet served at 37 °C, 42 °C, 47 °C, and 52 °C for 12 weeks.

Blood samples will be collected from each participant for analysis after 12-hour fasting, 3 times during the study (at the beginning and 6 and 12 weeks later).

Adipose tissue biopsies, protein isolation, and in vitro cell culture experiments will be performed as described elsewhere [33].

Cellular HSP-70 and HSP-90 levels will be measured to determine the thermic response to feeding, that is, evaluation of the causal relationship among higher dietary temperature, HSP-70/HSP-90 concentrations, and their time profile, as well as measures of obesity, aerobic fitness, resting metabolic rate, and diet-induced thermogenesis.

Food diaries will be analyzed using software to determine energy intake and macronutrient content.

An automated respirometer system plus a whole-body direct calorimeter, as the gold standard, will be used to measure energy expenditure and substrate utilization, aerobic fitness, resting metabolic rate, diet-induced thermogenesis, and markers of protein and fat catabolism to evaluate whether dietary temperature influences metabolism and surrogate end points of obesity in participants, such as weight and waist-hip ratio.

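### The two hottest arms are 49 and 54 °C in the allocation paragraph but 47 and 52 °C in Measures, so half the planned sample has two conflicting target temperatures

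*Protocol article*

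**What the plan says.** The serving temperature is described in five places in the protocol article.

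- *A Proposal to Conduct an RCT*: four arms, "diets served at different temperatures in 5 °C increments", with core body temperature as the reference.
- *Participants: Inclusion and Exclusion Criteria*: participants must have no limitation in swallowing food and drink over "a normally estimated range of meal temperatures (37-52 °C", closing bracket omitted.
- *Procedures*: boluses at "graded temperatures (eg, +5 °C increments) with a fair precision from 37 °C to 52 °C". The text calls this range ethical and "within the optimal drinking temperature of 57.8 °C".
- *Measures*: participants follow their "assigned diet served at 37 °C, 42 °C, 47 °C, and 52 °C for 12 weeks".
- *Sample Size Calculation*, allocation paragraph: 80 participants are randomised 1:1:1:1, with 20 at 37 °C, then "20 at 42 °C, 20 at 49 °C, and 20 at 54 °C".

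The 37 and 42 °C arms agree wherever arms are named. The third and fourth arms do not.

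**The concern.** Temperature is the only factor that separates the arms, so its levels are the treatment definition. Two explicit statements of those levels disagree for the two hottest arms.

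The allocation paragraph is the only place that attaches participant numbers to temperatures, so a randomisation list would naturally be built from it. The Measures section is the natural source for meal preparation. If each were followed as written, a participant allocated to 49 °C could be served soup at 47 °C, and any comparison or dose-response reading would be labelled with the wrong temperature.

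There is also a mismatch with eligibility. Under the allocation paragraph, 20 participants would eat soup at 54 °C, which is outside the range in the eligibility criterion and outside the range that Procedures calls ethical. The section on further technical issues describes soup at three meals a day for 12 weeks, so the exposure would be repeated.

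**Working it through.** No sample-size formula is involved. The check compares the stated arms with the design rule and with each other.

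**Step 1: participant count.** 4 arms × 20 = 80. This reproduces the stated total.

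**Step 2: arms implied by the design rule.** Four arms in 5 °C steps from 37 °C are 37 + 5i for i = 0, 1, 2, 3, which gives 37, 42, 47 and 52 °C. This equals the list in Measures and does not equal the list in the allocation paragraph. Taking 37 °C as core body temperature is consistent with both lists.

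**Step 3: side-by-side comparison.**

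| | Arm 1 | Arm 2 | Arm 3 | Arm 4 | Steps (°C) |
|---|---|---|---|---|---|
| Measures | 37 | 42 | 47 | 52 | 5, 5, 5 |
| Allocation paragraph | 37 | 42 | 49 | 54 | 5, 7, 5 |
| Difference | 0 | 0 | 2 | 2 | |

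**Step 4: participants affected.** Two arms × 20 = 40, and 40/80 = 50%.

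**Step 5: contrast with the 37 °C arm.**

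- Third arm: 49 − 37 = 12 °C against 47 − 37 = 10 °C; 12/10 = 1.20, a 20% larger contrast.
- Fourth arm: 54 − 37 = 17 °C against 52 − 37 = 15 °C; 17/15 = 1.13, a 13% larger contrast.

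These ratios describe the temperature contrast only. They say nothing about the size of any effect on an outcome.

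**Step 6: position against the stated limits.**

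- Range in the eligibility criterion and in Procedures, 37 to 52 °C: 49 °C lies inside it; 54 °C exceeds it by 54 − 52 = 2 °C.
- Cited optimal drinking temperature, 57.8 °C: 54 °C is 57.8 − 54 = 3.8 °C below it. Neither list exceeds this figure.

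**Step 7: is there a reason for 49 and 54 °C?** The Sample Size Calculation section quotes cell data at 37, 39, 42, 43 and 45 °C. None of 47, 49, 52 or 54 °C appears among them, so that material does not explain the change. The section remarks that food may be served over wider ranges, but it does not say that the arms were altered for that reason.

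**The case against.** The strongest reply is that this is an editorial slip in a hypothetical trial with no participants and no funding sought, and that a reader can easily infer the intended values. Four further points can be made.

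- Only Measures names 47 and 52 °C as arms. The design statement gives a step size, Procedures introduces its increments as an example, and the eligibility range excludes 54 °C but not 49 °C. This is correct. The firm contradiction is between Measures and the allocation paragraph, and the other three sections only corroborate.
- The eligibility criterion describes no thermal tolerance test, and 54 °C remains below the cited optimal drinking temperature. Procedures also says that optimum serving temperatures will be observed to avoid injury. This stands too: the text shows a 2 °C mismatch with the stated range, not a demonstrated hazard.
- The percentage differences have no proven bearing on outcome, since the quoted cell ratios rise and fall with temperature. This is fair, and the percentages are offered only as arithmetic on degrees above 37 °C.
- The total, the 1:1:1:1 ratio and the comparison with 37 °C are the same under either list, and unequal spacing is not in itself a statistical fault. Also true.

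None of this removes the contradiction. A slip in background text could be left alone, but this one sits in the definition of the randomised treatment. The article also invites replication in other populations, so the wrong figures could be carried forward. Condensation for a journal is no explanation, because nothing is missing: two explicit statements conflict.

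**Conclusion.** The concern holds, and the text must be corrected before the trial is run. Two of the four arms, 40 of 80 planned participants, have two target temperatures that differ by 2 °C. The allocation paragraph is the outlier: it breaks the 5 °C rule and puts the top arm 2 °C above the stated range, whereas 37/42/47/52 °C satisfies every other section.

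That 47 and 52 °C are the intended values is an inference from that agreement; the article does not say so. That the two lists conflict needs no assumption. The sample size is unaffected, and no breach of the 57.8 °C figure is claimed.

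**What to change.** In the allocation paragraph of Sample Size Calculation, replace 49 and 54 °C by 47 and 52 °C, so that 20 participants are allocated to each of 37, 42, 47 and 52 °C. This resolves the contradiction without touching any other section. The steps become 5, 5, 5 °C, the top arm falls within 37 to 52 °C, and the total stays 4 × 20 = 80.

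If 49 and 54 °C are intended, amend the design statement, Procedures and Measures, extend the eligibility range to 54 °C, and give the reason for the 7 °C step.

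The cost is two numbers. The Results section states that the trial has not been initiated, so no participants or data are affected.

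Two minor clarifications to Procedures could be made at the same time. They are separate from this point, and the verdict does not rest on them. First, state that the sentence "All drinks and a standardized diet will be served at room temperature" does not apply to the graded soup boluses. Second, explain how the expectation that "ingestion will be completed between 3 minutes and 5 minutes" fits with the instruction to consume meals as fast as is comfortable, and apply one pacing rule in all arms. The two pacing statements may be compatible if the minutes refer to a whole meal of several boluses, but the text does not say so.
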